## Methods/Design

The delivery of the SNAC protocol within the family practice unit using a brief 10-15 minute intervention geared to fit within a normal clinic session is critical to the potential implementation of the intervention in family practice. This follows previous developmental work with the STEP intervention which was found to be effective and acceptable to family physicians [19,37]. Training for the intervention will include a 30-minute workshop that promoted a team approach to identification of patients and delivery of the intervention by the family physician. The unit of analysis in SNAC is the individual patient, while the unit of randomization is the practice itself. Hence, it was deemed necessary to consider a cluster randomized, controlled design to determine the effectiveness of SNAC. Both STEP and SNAC have been endorsed by the College of Family Physicians of Canada.

The aim of this paper is to describe the design, features, and practicalities of the trial that may be common to other cluster randomized trials within a primary care setting.

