### Design

SNAC is a multicentre, cluster-randomized trial. Participating sites will include 20 clinical centres (6 academic family practices and remaining 14 non-academic centres). The Heart, Health, and Exercise Laboratory at the University of Western Ontario will serve as the central laboratory for all physiological and biochemical collections, and analyses. Recruitment of all clinical sites has been previously described with a catchment of over 150,000 patients [38]. The diet assessment and composition of the Mediterranean diet choices will be coordinated through Brescia College School of Nutrition at the University of Western Ontario, including quantification of dietary consumption using Food Processor (v 1.0). Serum measurement of free fatty acid levels (under the supervision of [name], University of Guelph) and measurement of endothelial markers of vascular function will be processed in the lipid analysis laboratory at McMaster University. Plasma leptin levels will be measured in the laboratory of [name] at the Exercise Nutrition Laboratory at the University of Western Ontario. The study has been funded by the Heart and Stroke Foundation of Canada and was approved by the Institutional Ethics Review Board of the University of Western Ontario.

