### Sample Size and Data Analysis

#### Sample Size

Data from a previous "feeding" trials including the DASH trial have estimated a standard deviation change in systolic blood pressure after the intervention was between 5.32 and 5.92 mmHg providing a 90% power [24]. In terms of change and blood glucose levels, 0.1 to 0.3 mmol. reduction are considered important in differentiation of the risk for the development of T2D [4]. For physiological outcomes' sample size estimate, we chose a mean difference between groups of 0.25 mm standard deviation as appropriate for change in vascular dimension. Previous work in our laboratory support the ability to detect the 2 mm difference in vessel diameter with a standard deviation of .025 mm following a similar lifestyle intervention. Hence, we required at least 10 subjects per group (two-tailed t-test, p < 0.025, power = 0.8). Assuming an 80% success rate in achieving suitable recordings in two test sites and a drop out rate of approximately 20%, we will recruit 40 subjects per treatment arm to the high normal blood pressure and IGT groups.

Initially, we anticipated recruiting about 5-10 patients per practice using a cluster design. To allow for the effect of this clustering we used an interpractice correlation coefficient (ICC) of 0.025. We felt this would be a conservative upper limit for the ICC on the basis of previous work in primary care. The inflation factor was therefore calculated to be 1+0.025 (10 minus 1) = 1.05. This figure gives a required number of patients per treatment arm of approximately 90 equivalent to 10 practices recruiting about 10 patients each.

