However, there is some theoretical loss of power from using variable cluster sizes. This is negligible in the current study of approximately 50 patients per treatment arm. Hence, our allocation method of 10 patients per practice was designed to avoid this possibility. Statistical analysis will include differences among the subjects' characteristics in clinical, behaivoural, and physiological outcome measures using analysis of variance (ANOVA). Interactions and/or a specific age, gender, or clinical variable differences will be examined using Tukey's post hoc analyses. If a group difference in a potentially confounding variable is observed at limit differences in a key outcome, analysis of covariance (ANCOVA) will be performed with the potentially confounding variable serving as the covariant. Relations of interest will be initially identified by univariate correlation analysis. Independent correlations among the dependent variables will be determined using partial correlation analyses and/or conventional multivariate step-wise regression analysis. In all cases, probability levels will be p < 0.05.

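### Practices are randomised, but the analysis named for the outcomes is ANOVA/ANCOVA with no term for practice; at the plan's own ICC a nominal 5% test then has a true size of about 6% to 8%

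*Protocol article*

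**What the plan says.** The Design section is explicit: "SNAC is a multicentre, cluster-randomized trial". Methods/Design adds: "The unit of analysis in SNAC is the individual patient, while the unit of randomization is the practice itself". The Randomization section likewise assigns practices to SNAC or usual care.

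Under Sample Size, the plan accepts that patients in one practice resemble each other: "To allow for the effect of this clustering we used an interpractice correlation coefficient (ICC) of 0.025". It regards this value as a cautious ceiling and uses it to inflate the number of patients. The ICC is put to no other use.

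The analysis paragraph that follows names ANOVA for "clinical, behaivoural, and physiological outcome measures using analysis of variance (ANOVA"). Tukey comparisons are named for interactions and subgroup differences. If a potential confounder differs between groups, "analysis of covariance (ANCOVA) will be performed with the potentially confounding variable serving as the covariant". Correlation and step-wise regression come next, and the paragraph ends: "In all cases, probability levels will be p < 0.05". No random effect for practice, generalised estimating equation, cluster-robust standard error or practice-level summary is mentioned anywhere. Practice setting appears as a subgroup factor (Secondary Outcome Measures) and as a stratification factor (Recruitment of Practices). Neither identifies the individual practice.

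**The concern.** Ordinary ANOVA and ANCOVA on patients take the patients as independent. The plan's own ICC says they are not. In a trial that randomises practices, variation between practices is part of the error of the arm comparison. A patient-level test without a practice term counts that variation as if it came from independent patients, so the standard error is too small, the confidence interval too narrow and the p-value too low.

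Enlarging the sample does not cure this. The inflation factor buys back power for an analysis that allows for clustering. It does not make an analysis that ignores clustering valid. At stake is the error rate of the between-arm comparisons, including the primary blood pressure, glucose, fitness and vascular outcomes.

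**Working it through.** **Inputs**
- ICC 0.025, and 10 practices of about 10 patients per arm: Sample Size.
- 20 practices in total: Design; Recruitment of Practices.
- Other cluster sizes: 5 to 10 per practice (Sample Size); 10 to 12 (Study Population); about 50 patients per arm in the analysis paragraph, that is 5 per practice; about 8 analysed if 10 are recruited and the plan's dropout of about 20% applies.
- Significance level 0.05. The analysis paragraph does not state sidedness, so two-sided is assumed.

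**The plan's own figure.** The design effect is DE = 1 + (m − 1) × ICC, with m patients per practice. The plan writes "The inflation factor was therefore calculated to be 1+0.025 (10 minus 1) = 1.05". The expression equals 1 + 0.025 × 9 = 1.225, so the printed 1.05 does not reproduce. It would need m = 3, or an ICC of 0.0056 at m = 10. This is a separate arithmetic error and the present point does not depend on it: even DE = 1.05 gives a true size of 5.6% by the formula below.

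**Standard error.** A patient-level test reports 1/√DE of the correct standard error. At m = 10 this is 1/√1.225 = 1/1.107 = 0.904, about 10% too small.

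**True size at nominal 5%.** Size = 2 × [1 − Φ(1.96/√DE)]. At ICC 0.025:

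| Patients per practice | DE | True size |
|---|---|---|
| 5 | 1.100 | 6.2% |
| 8 | 1.175 | 7.1% |
| 10 | 1.225 | 7.7% |
| 12 | 1.275 | 8.3% |

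**Check by simulation.** With 60,000 null trials per scenario and 10 equal practices per arm, the patient-level test rejected in 6.2%, 7.7% and 8.2% of trials for m = 5, 10 and 12. At m = 10, a t-test on the 20 practice means with 18 degrees of freedom rejected in 5.0%.

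**Sensitivity.** An ICC of 0.05 is an assumption, twice the plan's ceiling. At m = 10 it gives DE = 1.45 and a size of about 10%. An ICC of 0.01, also assumed, gives DE = 1.09 and about 6.0%.

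**Price of a valid analysis at ICC 0.025 and m = 10.** The standard error rises by a factor of 1.107. The critical value rises from 1.972 (198 degrees of freedom) to 2.101 (18), a factor of 2.101/1.972 = 1.065. Together: 1.107 × 1.065 = 1.18, so intervals are about 18% wider.

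**The case against.** The best defence is that the text is incomplete rather than wrong. The methods are introduced as things the analysis will include, which is not an exhaustive list, and no model terms are given at all, not even the arm. ANOVA can carry a nested random factor for practice. Naming the patient as unit of analysis fits a mixed model perfectly well. The abstract mentions the primary intention-to-treat comparison at 6, 12 and 24 months without naming a method, so tying the ANOVA sentence to it is a reading, though a natural one. A statistical analysis plan that is not shown might add the practice term.

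Part of this stands. A reader might infer that the plan deliberately rules out any allowance for clustering, or that the statement on the unit of analysis proves it. The documents do not go that far. But the article is not silent on analysis: it names the tests, the condition for covariate adjustment, the covariate and the significance level, and practice has no place in any of them. Followed as written, the plan gives standard errors that are too small.

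The size can also be overstated in two ways. A reader might conclude that the error rate is inflated for every outcome. That holds only where the outcome's own ICC is above zero, and the plan gives one planning value for all its outcomes. A reader might also quote sizes of 10% or more. Those need ICCs above the value the plan regards as its upper limit, and nothing in the documents supports them.

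**Conclusion.** The point holds. The analysis named for the outcomes has no term for the randomised unit, although the plan itself expects correlation within practices. At the plan's ICC of 0.025, a nominal two-sided 5% patient-level test has a true size of about 7.7% with 10 patients per practice, and between 6.2% and 8.3% across the cluster sizes the article mentions. The inflation is moderate but avoidable. It would be larger if an outcome's ICC exceeded 0.025.

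This rests on equal practice sizes, 10 practices per arm, two-sided testing, and reading the analysis paragraph as the method for between-arm comparisons.

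**What to change.** In the analysis paragraph of Sample Size and Data Analysis, state that between-arm comparisons use one of the following:
- a linear mixed model with a random intercept for practice and small-sample degrees of freedom (Kenward-Roger or Satterthwaite); or
- a t-test on the 20 practice means with 18 degrees of freedom.

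The patient can remain the unit of observation under the first option.

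The cost is wording only, with no new data. It would be wrong to expect intervals to widen by just the 11% that comes from the standard error. With 18 degrees of freedom the total is about 18% at ICC 0.025 and 10 per practice, with a matching loss of nominal power. The narrower intervals and higher power of the patient-level test were never available from 20 randomised practices.

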#### Secondary Outcome Measures

a) clinical - 24-hour ambulatory blood pressure; 2-hour glucose tolerance testing, hemoglobin A1C, microalbumin; waist circumference, calorie counts, b) behavioural measures - stage of change, self efficacy for diet and physical activity change, quality of life (SF36), barriers and benefits scales, c) physiological measures - waist circumference, calorie counts, dietary composition, cardiac function (echocardiographic determination of systolic and diastolic function, and left ventricular wall dimensions and volume), vascular geometry and elastic properties of the carotid and brachial arteries, muscle sympathetic and nerve activity discharge patterns at rest and a response to lower body negative pressure. Blood chemistry included blood lipid profiles homocystine, serum insulin, rennin, aldosterone, cortisol, C-reactive protein (CRP), markers of endothelial function including vascular adhesion molecule (VCAM) and intracellular cell adhesion molecule 1 (ICAM-1), urinary catecholamines, and serum free fatty acid composition.

Effects dependent on demographic subgroups will be defined by age, gender, and practice setting. Since previous trials have suggested that lifestyle interventions achieve their greatest effects early on, and that effects tended to diminish over time, we will evaluate the durability of these effects to 12 months and then for a further 12 months thereafter to determine the intervention rate of decay.

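### Interactions and subgroup differences are assigned to Tukey pairwise comparisons, which do not test effect modification; an arm-by-subgroup term should replace them

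*Protocol article*

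**What the plan says.** Under Secondary Outcome Measures, the protocol article commits the trial to subgroup effects: "Effects dependent on demographic subgroups will be defined by age, gender, and practice setting". No method is given there.

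The method comes in the analysis text under Sample Size and Data Analysis. Outcomes are to be compared by ANOVA, and the next sentence reads: "Interactions and/or a specific age, gender, or clinical variable differences will be examined using Tukey's post hoc analyses". ANCOVA is then reserved for potential confounders, and partial correlation and stepwise regression for associations. The text closes with a common threshold: "In all cases, probability levels will be p < 0.05".

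Tukey's procedure is thus the only tool named for interactions. No arm-by-subgroup term appears anywhere in the article. The Tukey sentence lists age, gender and clinical variables; practice setting appears only in the Secondary Outcome Measures sentence.

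**The concern.** Whether the intervention works differently in men and women is the question whether (SNAC minus control in men) minus (SNAC minus control in women) differs from zero. With two arms and two subgroups there are four cell means, and Tukey's method tests the six pairwise differences among them. None of the six is the contrast in question.

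The natural way to use the output is to note that the arms differ significantly in one subgroup and not in the other. That pattern is not evidence of effect modification. Each subgroup contrast has well under full power, so one of them often reaches significance alone by chance when the effect is the same in both.

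The article's Discussion anticipates a significant difference between arms and hopes to influence policy on lifestyle care. An apparent effect limited to one gender or age group could misdirect that use.

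**Working it through.** **Plan figures.** The article gives no number for its subgroup method, so there is none to reproduce. Its arm sizes disagree: 40, about 50, about 90, or 10 practices of about 10 (100). All four were therefore tried. Its inflation factor of 1.05 does not follow from its own formula, since 1 + 0.025 × 9 = 1.225. That is a separate matter and does not affect this point.

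**Inputs from the article.** Significance level 0.05; ICC 0.025; power of 80% (vessel dimension) and 90% (systolic pressure: "between 5.32 and 5.92 mmHg providing a 90% power").

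**Assumptions.** Two subgroups, split 50:50 or 70:30 (the article gives no shares); one true effect, identical in both; Tukey over four cells with no preceding interaction test.

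**Hand calculation, 50:50 split, 90% overall power.**
- Overall expected z = 1.96 + 1.28 = 3.24.
- In a half-size subgroup: 3.24/√2 = 2.29.
- Tukey critical |z| for four means, about 150 df: 2.60.
- Power in each subgroup: P(Z > 2.60 − 2.29) = P(Z > 0.31) = 0.38.
- Exactly one significant: 2 × 0.38 × 0.62 = 0.47.

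At 80% overall power: 1.96 + 0.84 = 2.80; 2.80/√2 = 1.98; P(Z > 0.62) = 0.268; 2 × 0.268 × 0.732 = 0.39.

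**Simulation.** 40,000 trials per scenario at 40, 50, 90 and 100 per arm. The Tukey columns give the percentage of trials with exactly one subgroup contrast significant; the last column gives the false-positive rate of the interaction test. Ranges run over the four arm sizes.

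| Overall power | Tukey, 50:50 | Tukey, 70:30 | Interaction test |
|---|---|---|---|
| No effect | 2.1 | 1.9-2.1 | 4.7-5.2 |
| 80% | 38.4-39.4 | 41.8-43.1 | 4.9-5.1 |
| 90% | 45.9-46.8 | 51.4-52.9 | 4.8-5.1 |
| 97% | 48.3-48.9 | 57.4-58.4 | 4.9-5.1 |

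With ICC 0.025 in the data (90 and 100 per arm, 50:50), the Tukey rate is about 38% at the effect set for 80% power, 44% at that for 90%, and 2.5-2.8% with no effect. The interaction test stays at 4.7-4.9%.

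Arm size hardly matters. At 80-90% power, 34-48% of trials show exactly one significant subgroup while the interaction test is not significant. A prior interaction test would remove those.

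**Power of the proper test.** With a 50:50 split, the standard error of the interaction contrast is twice that of the overall effect. For an interaction as large as an overall effect with 90% power, expected z = 3.24/2 = 1.62, and power = P(Z > 1.96 − 1.62) = P(Z > 0.34) = 0.37. For an overall effect with 80% power: 2.80/2 = 1.40; P(Z > 0.56) = 0.29.

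**Setting.** Arm and setting are both fixed per practice, so their interaction is a between-practice contrast. A patient-level test that ignores this understates its variance by the design effect. With 10 patients per practice that is 1.225, and the false-positive rate becomes P(|Z| > 1.96/√1.225) = P(|Z| > 1.77) = 0.077 instead of 0.05.

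**The case against.** The strongest reply is that a post hoc test follows an omnibus test. On that reading, a factorial ANOVA would test the interaction by its F-test and Tukey would only locate the differences. False interaction claims would then stay near 5% per test, and the 38-53% would not arise. This reading is possible, and it is why the figures must be conditional. But the text does not say it: the ANOVA sentence names no interaction, and the next sentence gives interactions to Tukey. The reading would also leave clustering by practice out of the model. For age and gender that matters little to the interaction test (4.7-4.9% above); for setting it matters.

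A second reply is that the sentence may partly concern baseline differences that could confound, since it stands between a sentence on subjects' characteristics and one on ANCOVA. That is fair for part of it, but the word for interactions remains.

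A third is that model terms are usually left to a full analysis plan. Here, though, a method is named that does not answer the stated question, and a plan that followed the sentence would carry the mismatch forward.

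Two stronger readings are tempting. A reader might infer that the trial will often report false subgroup effects. The article does not support that: it never says that significance in one subgroup only will count as effect modification, and with no treatment effect the rate is about 2%. A reader might also extend the calculation to three equal practice settings. Setting is not in the Tukey sentence, and the Design section gives 6 academic and 14 non-academic centres with no urban-rural split.

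**Conclusion.** The point holds as a defect in a stated secondary analysis. The method named for interactions does not test them, and nothing else in the article does.

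The size is conditional on three things: Tukey run without a prior interaction test, a real effect that is uniform across subgroups, and one-subgroup significance read as a subgroup effect. Under those conditions, with two subgroups split 50:50 to 70:30 and 80-90% overall power, about 38-53% of trials would look subgroup-specific, against about 5% for a direct test. The subgroup shares are assumed, and age would need cut-points that the article does not give before it formed such cells. Subgroup effects are listed under secondary outcomes, so neither the primary comparison nor the sample size depends on this.

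**What to change.** Replace the Tukey sentence. For age, gender and practice setting, add an arm-by-subgroup term to an outcome model with a practice random effect, and test that term. Judge the setting term against between-practice variation, with 20 practices in mind. Age can enter as a continuous variable, which avoids cut-points. Report the treatment effect with its 95% confidence interval in each subgroup, label these analyses exploratory, and state that power for interactions is low. If Tukey comparisons are kept, limit them to follow-up of a significant interaction.

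This costs a sentence or two of analysis wording and no extra data. The low power is not a price of the change, because it comes from the trial's size; the change only makes it visible.

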### Challenges with the intervention

Behaviour staging using the principles of the transtheoretical model has not been considered in many lifestyle intervention trials [29]. This in turn may have had impact on the long-term sustainability of changes that were observed. Previous lifestyle trials have also not consistently standardized the measurement or prescription of physical activity or dietary behavior [27,30-34]. Further, there has also been a lack of matching of physical activity to other lifestyle habits, such as dietary intake. Finally, whether the observed changes in behaviour and clinical outcomes are related to changes in basic physiological mechanisms that control health is also essential to understanding the impact of these interventions on the pathophysiology of hypertension and T2D.

In this setting of an epidemic of cardiovascular disease and poor lifestyle, the overall aim of the Staged Nutrition and Activity Counseling trial (SNAC) is to determine the blood pressure and blood glucose lowering effects of a matched or scaled physical activity and dietary lifestyle intervention among persons with high normal blood pressure and/or impaired glucose tolerance. Further, as most of these patients are seen in family practice, and given the key role family physicians may provide in achieving and sustaining lifestyle change, the intervention will be delivered compared to the usual care of family practice lifestyle management. Finally, few studies have suggested that lifestyle interventions (primarily single interventions) can improve physiological determinants of cardiovascular function and health [35,36]. Whether this is similar in a large primary care intervention with two simultaneous lifestyle interventions is unknown. It is anticipated that the results of SNAC will provide scientific rationale and guidance for the implementation of this important lifestyle intervention program designed to prevent hypertension and T2D among those at risk for cardiovascular disease.

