## Discussion

The health benefits and implications of the SNAC lifestyle intervention could be substantial. In patients with a high risk for hypertension and T2D, each component of the SNAC intervention, including increasing physical activity and alteration of dietary intake, have been shown to reduce blood pressure and blood glucose in previous studies. However, a lack of implementation of these interventions using tailored primary care approaches has restricted the impact. The net effect of these small improvements in clinical variables can have quite significant effects on the prevention of hypertension and T2D, and hence cardiovascular risk [46]. Hence, the effects of the SNAC intervention on cardiovascular outcomes could be impressive.

It has been suggested that a population-wide approach of the DASH dietary pattern could reduce the incidence of coronary heart disease by 15% and stroke by 27% in U.S. adults just from BP reduction alone [47]. We suggest that the net effect of SNAC could be substantiately greater due to a combined lifestyle intervention but also, since the adherence and implementation to such a program could be greater through delivery in a family practice setting this seems even more likely than was observed in previous studies [48]. Further, we will identify the underlying behavioral and physiological determinants of these clinical changes. This will improve our understanding of the global improvement in patient cardiovascular risk.

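### The univariate screen for determinants of clinical change has no treatment term and the next step commits to none, so correlations pooled over arms can partly reflect SNAC's shared effect

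*Protocol article*

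**What the plan says.** The statistical paragraph under Sample Size and Data Analysis sets out a two-step search for relations between variables. The first step: "Relations of interest will be initially identified by univariate correlation analysis". The second: "Independent correlations among the dependent variables will be determined using partial correlation analyses and/or conventional multivariate step-wise regression analysis". The threshold is common to all analyses: "In all cases, probability levels will be p < 0.05".

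Two other sections give the purpose. Challenges with the intervention raises the question "whether the observed changes in behaviour and clinical outcomes are related to changes in basic physiological mechanisms that control health", and the Discussion promises that "we will identify the underlying behavioral and physiological determinants of these clinical changes".

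Treatment arm is named in neither step, and nothing says that the correlations are computed within arm. The ANCOVA in the same paragraph is reserved for variables that confound a group difference, so it does not cover these analyses.

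**The concern.** SNAC is meant to move many outcomes together: blood pressure, glucose, fitness, BMI, vascular function and diet. In a sample pooled over arms, two outcomes that both respond to SNAC differ between the arms in step. That alone produces a correlation between them, even if patients within an arm show no relation at all. Arm acts as a common cause.

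This differs from the familiar problems of multiple testing and stepwise selection. It persists if a single pair of variables is pre-specified and if the p-values are corrected.

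At stake is the mechanistic conclusion. A variable could be called a determinant of clinical change because SNAC also moved it, and the risk rises with SNAC's effect.

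**Working it through.** The article gives no figure for the correlation analysis, so there is none to reproduce. The check asks how large the induced correlation is and how often it would reach p < 0.05.

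**Inputs**

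- Threshold: p < 0.05, taken as two-sided.
- Sample size: the article gives three unreconciled figures. They are "we will recruit 40 subjects per treatment arm" (80 in total), "negligible in the current study of approximately 50 patients per treatment arm" (100) and "This figure gives a required number of patients per treatment arm of approximately 90" (180). Applying the article's 80% recording success and 20% drop-out to 80 patients gives 80 × 0.8 × 0.8 = 51.2, taken as 52 for two equal arms. The range is therefore 52 to 180.
- Standardised effects of SNAC: assumptions. The article gives an SD for systolic change but no target difference, hence no standardised clinical effect. Values of 0.3, 0.5 and 0.8 SD are shown.
- A large vascular effect: 10 per group at two-sided 0.025 and 80% power corresponds to (2.241 + 0.842) × √(2/10) = 1.38 SD by the normal approximation, or 1.48 SD by the t-test. This is a detectable effect worked back from the sample size, not an expected one. The same paragraph quotes a 2 mm difference with SD 0.025 mm, which is 80 SD and cannot be reconciled with it. So 1.48 is only an illustration of a large effect.

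**Induced correlation**

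With 1:1 arms, zero correlation within arm, and effects d1 and d2 in within-arm SD units:

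r = (d1·d2/4) / √[(1 + d1²/4)(1 + d2²/4)]

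- 0.3 and 0.3: 0.0225 / 1.0225 = 0.022
- 0.5 and 0.5: 0.0625 / 1.0625 = 0.059
- 0.8 and 0.8: 0.16 / 1.16 = 0.138
- 1.48 and 0.5: 0.185 / √(1.5476 × 1.0625) = 0.144

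The r needed for p < 0.05 is 0.273 with 52 patients, 0.220 with 80, 0.197 with 100 and 0.146 with 180.

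**How often an unrelated pair is declared related** (simulation, 40,000 runs per cell, independent patients)

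| Effects (SD) | n=52 | n=80 | n=100 | n=160 | n=180 |
|---|---|---|---|---|---|
| 0.3 / 0.3 | 5% | 6% | 6% | 6% | 6% |
| 0.5 / 0.5 | 7% | 8% | 9% | 11% | 12% |
| 0.8 / 0.8 | 16% | 23% | 28% | 42% | 46% |
| 1.48 / 0.3 | 9% | 12% | 14% | 20% | 22% |
| 1.48 / 0.5 | 18% | 25% | 30% | 45% | 49% |

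Separate runs agree to within one or two points; for 0.5/0.5 at 180 they gave up to 12.6%. With arm partialled out, every cell is 4.8–5.2%. Adding the article's ICC of 0.025 in runs with 80 to 200 patients and equal effects on both outcomes changed the rates by about one point or less.

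**Does the second step remove it?** Only if arm is in it. For 1.48/0.5 with 160 patients, partialling out one other outcome shifted by 0.5 SD lowers the rate from 45% to 41%, and partialling out three lowers it to 35%. Other outcomes are weak stand-ins for arm.

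**The case against.** The strongest reply is that much of this rests on silence. The article does not say that the correlations are pooled over arms, and the partial-correlation or stepwise step names no conditioning variables. A reader might infer that arm is excluded from that second step. The text does not support this: it neither includes nor excludes arm, and a full protocol or SAP may settle it. The relations of interest might also be baseline relations, which carry no treatment effect, and the promise about determinants stands in the Discussion, not beside the method. All of this limits the claim. What survives is that the first step is a stated method that cannot carry a treatment term, that the second does not commit to one, and that pooling over arms is the natural, though not express, reading.

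A reader might also infer that any two outcomes moved by SNAC will look related. The numbers contradict this: at 0.3 SD the error rate is essentially nominal, and at 0.5 SD on both outcomes about 87% or more of unrelated pairs still fail to reach significance.

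The objection to 1.48 SD also stands. It comes from an inconsistent vascular calculation and applies to one type of measure. The 0.8 SD row shows that a material distortion does not depend on it.

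Finally, these are secondary analyses, and adjusting for arm does not prove mechanism, because unmeasured patient factors remain. Both points are accepted. They limit the weight of the issue without removing it.

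**Conclusion.** The point holds in a limited form. The screening correlation has no treatment term, and the step after it does not commit to one. If changes are pooled over arms, the resulting associations mix SNAC's shared effect with any relation among patients within an arm, although the article intends to name determinants of clinical change.

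Over 52 to 180 patients the distortion is negligible for small effects (0.3 SD on both outcomes), modest at 0.5 SD on both, and material when effects are large, as with 0.8 SD on both or a very large effect paired with a moderate one. These results assume pooling, equal arms, no within-arm correlation and the stated effect sizes, none of which the article fixes for clinical outcomes.

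The randomised comparison of SNAC with usual care is not affected. This is worth correcting before analysis but does not threaten the trial's main result.

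**What to change.** State in the analysis text that, for any relation between post-baseline outcomes or changes:

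- treatment arm is included in both the screening step and the partial-correlation or regression step, or the correlation is computed within arm;
- the arm-adjusted association is the reported result;
- no variable is called a determinant on a pooled, unadjusted correlation.

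Relations among baseline values need no change. A random effect for practice is optional and not needed for this point.

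The cost is one model term and a sentence or two of wording. No extra data, visits or patients are required.
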